**Fig. 2 Fig2:**
[figure not shown]
Acupuncture treatment schedule and ANS measurement. *ASQ* indicates acupuncture sensation questionnaire, *BTQ1* blinding test questionnaire1

#### Acupuncture treatment setting and equipment

The acupuncture treatment room setting will be modified from a previous study by Lee et al. [5] and is shown in Fig. 3. Participants will lie on the bed in a supine position. A visual barrier will prevent participants from viewing their leg and the acupuncture treatment procedure directly.

**Fig. 3 Fig3:**
[figure not shown]
Acupuncture treatment setting

Acupuncture stimulation will be recorded simultaneously and will be shown to the participants through a ceiling monitor in real time for 3 min. Before the stabilization phase, the operator will show the acupuncture point and movement of their legs through the ceiling monitor so that participants will have body ownership via the image.

Details of the acupuncture treatment plans are shown in Table 1.

**Table 1 Tab1:** Details of acupuncture treatments (STRICTA 2010 checklist)

Item		Detail
1. Acupuncture rationale	1a) Style of acupuncture	Manual acupuncture based on traditional Korean medicine theory
	1b)Reasoning for treatment provided, based on historical context, literature sources, and/or consensus methods, with references where appropriate	Consensus of the KMD
	1c)Extent to which treatment was varied	All participants will receive standardized treatment
2. Details of needling	2a) Number of needle insertions per subject per session	1
	2b) Names of points used	Left ST36
	2c) Depth of insertion, based on a specified unit of measurement	15 mm
	2d) Response sought	De-qi
	2e) Needle stimulation :	During 3 min of phasic session, manual stimulation will be conducted eight times based on an audio signal received via a headphone. Interval between each manual stimulation is from 10 to 14 s. For each manual stimulation, the acupuncture needle will be rotated five times during 3 s.
	2f) Needle retention time	11 min
	2g) Needle type	[Group 1] Real Streitberger’s needle; 0.25 × 40 mm sterilized stainless steel needle (Asia-med GmbH & Co. KG, [name], Germany).
		[Group 2] PSD; 0.25 × 40 mm sterilized stainless steel needle (Park sham Device, Acuprime, Exter, UK).
3. Treatment regimen	3a) Number of treatment sessions	3 sessions
	3b) Frequency and duration of treatment sessions	3 sessions for 1 day
		(30 min washout period between each session)
4. Other components of treatment	4a) Details of other interventions administered to the acupuncture group	None
	4b) Setting and context of treatment, including instructions to practitioners, and information and explanations to patients	The study will be conducted in the Kyung Hee University Medical Center. All information except the objective of trial and acupuncture types will be provided to the participants.
5. Practitioner background	5) Description of participating acupuncturists	Licensed KMD with at least 5 years of clinical practice experience
6. Control interventions	6a) Rationale for the control or comparator in the context of the research question, with sources that justify this choice	Validated placebo acupuncture devices will be used in control sessions.
	6b) Precise description of the control or comparator. If sham acupuncture or any other type of acupuncture-like control is used, provide details as for Items 1 to 3 above.	The order of three treatments in each group will be randomized.
		[GROUP 1] 1) Sham Streitberger’ needle: 0.25 × 40 mm sterilized stainless steel needle (Special No. 16 of Asia-med GmbH & Co. KG, [name],Germany) will be used. The appearance, acupuncture point, stimulation method, and duration will be the same with the real Streitberger’s needle.
		2) Phantom acupuncture: There is no tactile stimulation to ST 36. To induce credibility that participants are treated with acupuncture, the video clip of the previously recorded Streitberger’s needle session will be shown.
		[GROUP 2] 1) PSD with sham needle: 0.25 × 40 mm sterilized stainless steel needle (Park sham Device, Acuprime, Exter, UK) will be used. The appearance, acupuncture point, stimulation method, and depth will be the same with the PSD as with the real needle. 2) No treatment: There is no acupuncture treatment. To induce the attention effect as in the other sessions, a neutral image will be provided instead of an acupuncture treatment image.

*KMD* Korean Medicine Doctor; *PSD* park sham device

#### Phantom acupuncture and no treatment session

In PHNT, practitioners will not provide any tactile stimulation and will only approach their hand to the left ST 36 acupuncture point without touching. A recorded video clip of the participant’s Real ST session will be played during the PHNT session. If the PHNT session is scheduled as the first session, we will play a video from another participant with similar skin color and leg hair.

In the No treatment session, practitioners will inform participants that they will not receive any treatment. A blinding questionnaire will not be completed; recorded physiological data will be used as a baseline. In order to ensure comparability, participants will undergo the same procedure except they will be shown a 3 min video clip that is not related to acupuncture but has a similar background color and shows some type of artificial movement that would occur with same stimulation time point during an acupuncture session.

### Outcome measurement

#### Primary endpoint

BTQ 1 : After each acupuncture session, participants will complete the BTQ 1. BTQ1 consists of five questions. If a participant completes all five questions without any doubt or asking, we will conclude blinding is succeeded. If participants mention strange aspect of the questionnaire or reply they did not receive acupuncture treatment, conclude that blinding is failed. Otherwise, we will conclude that blinding is succeeded.

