### Sample size calculation

This will be a kind of mechanism study, so we did not follow the general method to calculate sample size. It is known that a sample size of 12 or more is adequate for a pilot study [15, 16]. We concluded that we will have sufficient analytical power if our sample size is greater than 12. We decided that we need to enroll at least 30 participants in our pilot study for each session assuming a drop-out rate of approximately 20 %. We calculated a sample size of 37.5 and rounded to this to 38 resulting in a total sample size of 76 participants.

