### Statistical analysis

As our design has two independent groups that acquire comparability by randomization, we can compare variables not only within each group, but also between groups.

The primary outcome of our research will be to compare the blinding rates of the placebo acupuncture devices studied within and between groups. We will also conduct several exploratory secondary outcome analyses. Expectation for acupuncture (measured by AEQ) [6], previous acupuncture experiences, and age will be considered as covariates. We will analyze physiological data in three tonic responses (before, during, and after acupuncture) and during phasic responses. We will not statistically compare the Bang’s BI [9]. Instead, we will calculate the point estimate and 95 % confidence interval of Bang’s BI.

For dichotomous variables (i.e., blinding rate), within group comparison will be performed using Cochran’s Q test for Group 1 (Sham ST, Real ST, and PHNT) and McNemar’s test for Group 2 (Sham, Real Park). We will not check the blinding of the No treatment session. Comparisons of blinding rates between group devices (Sham ST vs Sham Park or PHNT vs Sham Park) will be performed using the chi-square test, and comparisons within group devices (PHNT vs Sham ST) will be performed using McNemar’s test. For continuous variables (i.e., the MASS index, De-qi sensation, physiological data such as HR, HRV, and SCR), within group comparisons will be performed using repeated measured ANOVA for Group 1 and paired *t*-test for Group 2. We will use the independent *t* test for comparisons between group.

When we analyze physiological data, we will use the both change ratio contrast to baseline and absolute value. Change ratio and absolute value of HR and SCR will be compared for three separate windows during the tonic responses (before vs during vs after acupuncture session). As absolute change value is very dependent on baseline value, it will be used as covariates.

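### The closing default in the primary-endpoint rule makes its own success condition inoperative, and one kind of answer meets both the success and the failure rule

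*Protocol article*

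**What the plan says.** The rule stands in the protocol article under Primary endpoint. The form is given after every acupuncture session: "After each acupuncture session, participants will complete the BTQ 1". Three sentences then classify each participant:

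- Success: "If a participant completes all five questions without any doubt or asking, we will conclude blinding is succeeded".
- Failure: "If participants mention strange aspect of the questionnaire or reply they did not receive acupuncture treatment, conclude that blinding is failed".
- Everyone else: "Otherwise, we will conclude that blinding is succeeded".

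Under Statistical analysis, the primary aim is to "compare the blinding rates of the placebo acupuncture devices studied within and between groups", using Cochran's Q, McNemar's test and the chi-square test. One session is exempt: "We will not check the blinding of the No treatment session". Five sessions therefore yield a blinding rate. Bang's blinding index is estimated with a confidence interval but is not tested.

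**The concern.** A success condition that mentions doubt and asking implies that these count against success. The default then hands success to the very people who missed that condition. The second problem is an overlap: a confident reply that no acupuncture was given can come from someone who completes all five items without hesitation, and so satisfies both the first and the second sentence. This is easiest to imagine in the phantom session, where nothing touches the skin.

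The stakes are those of the primary endpoint. Participants learn that placebo was used only after the last session, so spontaneous doubt is one of the few signals BTQ 1 can pick up. The failure trigger for remarks is tied to the questionnaire. Read literally, someone who finds the needling odd, or asks whether it was genuine, without saying that no acupuncture was given, is scored as blinded. Every formal comparison of blinding in the article rests on this classification.

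**Working it through.** **1. The plan's own figure.** Sample size calculation says "we need to enroll at least 30 participants in our pilot study for each session", "assuming a drop-out rate of approximately 20" per cent. 30 / (1 − 0.20) = 37.5, rounded up to 38 per group, and 2 × 38 = 76. The stated total is reproduced and is not affected by this point. It supplies the two values of n used below.

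**2. The rule applied to each kind of participant.**

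| Participant | Success sentence | Failure sentence | Default | Result |
|---|---|---|---|---|
| All five items, no doubt, no trigger | met | no | not needed | success |
| Doubt or asking, no trigger | not met | no | applies | success |
| Form incomplete, no trigger (literal reading) | not met | no | applies | success |
| Doubt or an incomplete form, with a failure trigger | not met | met | no | failure |
| All five items, no doubt, replies that no acupuncture was given | met | met | no | undetermined |

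Deleting the success sentence would change no row except the last, where it would remove the conflict. In effect the rule is: success unless a failure trigger occurs.

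**3. Size for one device.** Let n be the evaluable participants, r those in the residual group (doubt or asking, no trigger), and f the share of clear failures.

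Rate under the default = 1 − f. Rate with the residual counted as failed = 1 − f − r/n. Difference = r/n.

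| r | n = 30 | n = 38 |
|---|---|---|
| 0 | 0.0 points | 0.0 points |
| 1 | 3.3 | 2.6 |
| 3 | 10.0 | 7.9 |
| 6 | 20.0 | 15.8 |

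The values of r are assumptions. A participant in the last row of step 2 likewise moves the rate by 1/n, according to how that overlap is resolved.

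**4. Size for a comparison of devices A and B.** Write r_A/n and r_B/n for the residual shares. Moving from the default to counting the residual as failed changes the difference (A − B) by r_B/n − r_A/n. Equal shares cancel.

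Illustration, with assumed rates, 10% clear failures for both devices, n = 30 each and a two-sided alpha of 0.05 (the article states no alpha):

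- Residual 10% and 10%: 90% v 90% under the default, 80% v 80% otherwise. The difference is unchanged.
- Residual 20% and 5%: 90% v 90% under the default, 70% v 85% otherwise. Power to detect the latter is about 28%.
- Residual 30% and 5%: 90% v 90% under the default, 60% v 85% otherwise. Power is about 59%.

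In the last two cases the default shows no difference at all.

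**The case against.** The strongest reply is that doubt and mentioning something strange may be meant as the same behaviour. Doubt voiced as a remark on the questionnaire, or as a reply that no acupuncture was given, is already a failure, so the residual group could be small or empty. This stands as a limit on size. It does not rescue the wording: if the residual is empty the default is unnecessary, and if it is not, the default overrides the success condition.

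Nor is asking the same as being unblinded. A participant who wants an item explained has revealed nothing about the treatment, and counting every question as a failure could bias the rate downwards. This also stands, and the fix allows for it.

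On incomplete forms, the article says only that participants will complete BTQ 1. Scoring a partial form as success is the literal effect of the default, not an explicit provision, and missing-data handling may lie in a fuller document. No figure above depends on it.

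The overlap can be read sensibly, with the specific failure reply taking precedence. That is probably the intention, but the text does not say so.

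Bang's blinding index is a separate look at unblinding. It does not repair the primary endpoint, and the plan does not test it.

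**Conclusion.** The rule is inconsistent in effect: its first condition is inoperative, and one combination of answers is both success and failure. This is a rule the article states, not a detail it leaves out. Relative to counting the residual group as failed, the default can only raise a device's rate, by r/n. That is 3.3 points per participant at n = 30 and 2.6 at n = 38, with r not given and possibly zero. It can hide a difference between devices when residual shares differ.

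A reader might go further in three ways that the documents do not support:

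- That everyone who voices doubt is counted as blinded. Some forms of doubt are already failures.
- That every device's rate is inflated and the placebo-versus-real contrast shrinks. The article gives no frequency of doubt by session, equal shares cancel, and the excess is a true overstatement only if the residual participants were in fact unblinded.
- That assumed shares of doubt and of incomplete forms can simply be added, so that 10% and 5% give 15 points. If incomplete forms are treated as missing, 70% clear successes give 0.85 under the default against 0.70 / 0.95 = 0.737, about 11 points, and both shares remain assumptions.

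**What to change.** Replace the three sentences with one ordered, exhaustive rule:

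1. Failed if the participant replies that no acupuncture was given or mentions something strange. This overrides all else. State whether it covers the session as well as the questionnaire.
2. Success only if all five items are completed without doubt or asking about the treatment.
3. Residual doubt, or asking whether the treatment was genuine, is not a success in the primary analysis. A sensitivity analysis counts it as success. Requests to clarify an item do not fall here.
4. An incomplete or absent BTQ 1 without a failure trigger is missing, not success.

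Add a field to the form that records doubt or asking and what was said, so that the rule can be applied.

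The cost is one paragraph and one field. Reported blinding rates may be slightly lower. Because the trial is recruiting, this changes the primary-endpoint definition during conduct and must be documented before any classification. Sessions already completed can be reclassified only if doubt or asking was recorded, which the article does not say. If it was not, report those sessions under the present rule and say so.

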#### Secondary endpoints

##### Bang’s blinding index (BI)

After all the sessions are finished, participants will complete the BTQ 2. At this time, participants will be told that a placebo acupuncture session occurred. We will calculate the BI from the BTQ 2 [7]. The range of BI is −100 to 100 %; 0 % means random guessing (e.g., 50 % correct and 50 % incorrect) and 100 % means complete unblinding (i.e., all responses are correct), −100 % means opposite of guessing (e.g., all responses are incorrect) [8]. Thus, the BI is the proportion of participants who guessed their treatment arm correctly beyond chance [9, 10].

##### Massachusetts General Hospital (MGH) Acupuncture Sensation Scale (MASS) Index by de-qi sensation questionnaire (DSQ)

The MASS measures the sensation caused by acupuncture stimulation. It consists of 12 descriptions: soreness, aching, deep pressure, heaviness, fullness/distention, tingling, numbness, sharp pain, dull pain, warmth, cold, and throbbing. The MASS index is a weighted average based on a formula [11]. We will determine the MASS using the DSQ.

##### Heart rate, heart rate variability, and skin conductance response

Participants will rest for 5 to10 min before we measure their tonic response to stabilize the electrocardiogram and SCR wave pattern. We will record the HR and SCR throughout the study using a PowerLab Data acquisition system/800, Bio amplifier/ML132, GSR Amplifier/ML116 (AD instruments, Australia) with a 400 Hz sampling rate. To measure HR, participants will be placed on the bed and three electrodes (3M disposable PAD 2223) will be attached beneath the clavicles and the left rib. Then, we will remove power noise frequency at 60 Hz and detect the R peak to measure the HR. To measure the SCR, we will apply a gel to the index and third fingers and attach electrodes [5, 12].

The HR and SCR will be measured during the tonic and phasic responses. For the tonic responses, the mean HR and SCR will be measured before, during, and after the acupuncture treatment session for 5 min.

The HRV will be calculated by evaluating the R peak. In the time domain analysis, we will calculate the standard deviation of all R-R intervals (SDNN) and the root-mean-square of the successive difference (RMS-SD). For the frequency domain analysis, we will calculate the high frequency value (HF), low frequency value (LF), total power, and the LF/HF ratio [13, 14].

In the phasic event related SCR responses, the average of the maximum score change and the area under the curve (AUC) will be estimated. We will also calculate the stimulation/baseline SCR ratio of the score change and the AUC.

### Sample size calculation

This will be a kind of mechanism study, so we did not follow the general method to calculate sample size. It is known that a sample size of 12 or more is adequate for a pilot study [15, 16]. We concluded that we will have sufficient analytical power if our sample size is greater than 12. We decided that we need to enroll at least 30 participants in our pilot study for each session assuming a drop-out rate of approximately 20 %. We calculated a sample size of 37.5 and rounded to this to 38 resulting in a total sample size of 76 participants.

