**Methods/Design:**

The proposed study is a single-center prospective random sequence participant- and assessor-blinded trial with two parallel arms. A total of 76 participants will be randomly assigned to Group 1 or Group 2 in a 1:1 ratio. Group 1 will consist of Sham Streitberger’s needle, Real Streitberger’s needle, and Phantom acupuncture session. Group 2 will consist of Park Sham device with real needle, Park Sham device with sham needle, and no treatment session. Participants will have a total of three acupuncture sessions in a day. The primary endpoint is blinding test questionnaire 1. Secondary endpoints are the Bang’s blinding index, the Massachusetts General Hospital Acupuncture Sensation Scale index, and physiological data including heart rate, heart rate variability, and skin conductance response.

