## Methods/Design

### Objectives

The objectives of this trial are to evaluate the validity of different types of placebo acupuncture devices and determine their suitability for use as placebos in clinical trials.

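### Sufficient power is claimed for any sample above 12 from a pilot-size rule of thumb: wrong just above 12 for all but extreme differences, and unsupported at the planned 30

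*Protocol article*

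**What the plan says.** The Protocol article, Sample size calculation, opens by setting the usual approach aside: "This will be a kind of mechanism study, so we did not follow the general method to calculate sample size". It then cites a rule of thumb, "It is known that a sample size of 12 or more is adequate for a pilot study", and concludes from it: "We concluded that we will have sufficient analytical power if our sample size is greater than 12". Next it asks for "at least 30 participants in our pilot study for each session assuming a drop-out rate of approximately 20" per cent, and ends: "We calculated a sample size of 37.5 and rounded to this to 38 resulting in a total sample size of 76 participants". No significance level, expected blinding rate, difference to detect, test or power value is given.

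The Statistical analysis section makes the primary analysis comparative: "The primary outcome of our research will be to compare the blinding rates of the placebo acupuncture devices studied within and between groups". The tests named are Cochran's Q for the three Group 1 sessions, McNemar's test for paired comparisons, and the chi-square test between groups. That section calls only the secondary analyses exploratory. The Objectives section sets a confirmatory-sounding aim, to "evaluate the validity of different types of placebo acupuncture devices and determine their suitability for use as placebos in clinical trials".

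**The concern.** A recommendation that 12 is enough for a pilot concerns feasibility or rough estimation. It says nothing about the chance that a McNemar, Cochran's Q or chi-square test will detect a given difference in blinding rates. The sentence nevertheless asserts power, and for every sample size above 12.

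The direction of the error matters here. In a placebo-validation study the favourable result of a real-versus-sham comparison is no significant difference, and the Discussion says the trial will investigate whether the placebo techniques can be told apart from real needling. A reader who accepts the power statement has grounds to treat a non-significant blinding comparison as evidence that the device blinds well. If power is low, that reading is unsafe.

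**Working it through.** **The plan's own figure.** 30 evaluable per session with 20% drop-out: 30 / (1 − 0.20) = 37.5, rounded up to 38 per group; 2 × 38 = 76. This reproduces exactly. The power statement cannot be reproduced, because it carries no inputs.

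**Inputs assumed, since the document gives none.** Two-sided alpha 0.05; 80% power as benchmark; blinding success 95% for the better device and 75% for the worse (a 20-point gap), with other gaps shown. For paired tests, two extremes of within-person dependence:
- Independent answers: P(success on the better device only) = 0.95 × 0.25 = 0.2375; P(success on the worse only) = 0.05 × 0.75 = 0.0375; discordant total 0.275.
- Maximal positive correlation (about 0.40 for these rates): 0.20 and 0; discordant total 0.20.

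**Tests, with power found by enumerating all outcomes.**
- Chi-square, n per group: (p̂₁ − p̂₂)² / [p̄(1 − p̄)(2/n)] > 3.84.
- McNemar asymptotic: (b − c)² / (b + c) > 3.84, with b and c the two discordant counts.
- McNemar exact: two-sided binomial on b out of b + c. With 5 discordant pairs the smallest p is 2 × 0.5⁵ = 0.0625, and with 6 it is 2 × 0.5⁶ = 0.031, so at least 6 discordant pairs are needed.

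At n = 13 the expected number of discordant pairs is 13 × 0.275 = 3.6 (independent) or 13 × 0.20 = 2.6 (maximal correlation), well short of 6. At n = 30 it is 8.25 or 6.0.

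**Power for 95% against 75%:**

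| n | Chi-square (n per group) | McNemar, independent (exact / asymptotic) | McNemar, maximal correlation (exact / asymptotic) |
|---|---|---|---|
| 13 | 24% | 4.7% / 25.0% | 3.0% / 25.3% |
| 30 | 63% | 44% / 58% | 57% / 88% |

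Intermediate correlations at n = 30 give 50% / 70% (correlation 0.2) and 55% / 83% (correlation 0.35). At n = 13 the highest value is 25.6%, at correlation 0.2.

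**Gap from 95% that gives 80% power:**
- Chi-square, n = 13 per group: about 45 points (80.1%).
- Chi-square, n = 30 per group: about 26 points (80.2%).
- McNemar, n = 30, independent: about 28 points asymptotic (81.2%), 31 exact (80.2%).
- McNemar, n = 30, maximal correlation: about 18 points asymptotic (81.4%), 25 to 26 exact (79.7%, 83.0%).

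**Cochran's Q (simulation, latent correlation 0 and 0.5).** Success rates of 95/85/75% give 16% to 20% at n = 12 and 48% to 60% at n = 30. Rates of 95/90/60% give 53% to 65% and 93% to 98%.

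**Precision of a null result.** If both devices truly blind 90% and each group has 30, the 95% confidence interval for the between-group difference has half-width 1.96 × √(2 × 0.9 × 0.1 / 30) = 0.15, about 15 points.

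**The case against.** The section says openly that no conventional calculation was made and calls the work a mechanism and pilot study, so a careful reader is warned. The number 12 does not set enrolment; 30 does. Both points stand, and they limit the matter to what is claimed rather than how many are recruited. They do not rescue the sentence, which still asserts a power property that its premise cannot supply.

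A reader might go further and infer that the claim is also false at 30. The documents do not support that. Power is adequate or not only against a target difference, and none is fixed. At 30 per group the chi-square test has 94% power for 95% against 60%, and about 80% for 90% against 60%.

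Nor do the figures support saying that important gaps would generally be missed half the time or more at 30. For the 20-point gap the chi-square test misses 37%. With independent pairs McNemar misses 42% (asymptotic) or 56% (exact), so only the exact version passes one half. The Statistical analysis section does not say which version applies, and the document names no gap that would disqualify a placebo. Each participant answers the same questionnaire after successive sessions on one day, so positive correlation is plausible, and it raises paired power at this size.

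The width of the confidence interval for Bang's index does not bear on the primary tests: that index is secondary and the plan says it will not be compared statistically.

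**Conclusion.** The sentence claiming sufficient power should not stand. Just above 12 it is wrong for all but extreme differences: 3% to 26% (McNemar) and 24% (chi-square) for 95% against 75%, with a chi-square gap of about 45 points needed for 80%. Even in the most favourable paired setting examined at n = 12 (90% against 50%, maximal correlation, asymptotic test), McNemar's power is 78%.

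At 30 per session the claim is unsupported. Power is 63% (chi-square) or 44% to 88% (McNemar) for a 20-point gap, and 80% is reached at about 26 points (chi-square) or 18 to 31 points (McNemar). All these figures rest on an assumed 95% rate for the better device and two-sided 0.05. The McNemar ranges also reflect the unknown correlation and unspecified test version.

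Nothing here shows that 76 is miscalculated. Nor does the document state that a non-significant test will be taken as proof of indistinguishability; the point is that the power claim invites that reading.

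**What to change.** In the sample size section:

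1. Delete the sentence claiming sufficient power above 12.
2. State that 30 evaluable participants per session was not derived from a power calculation.
3. Give what 30 can detect, with assumptions. For example: *With 30 evaluable participants per session, two-sided 0.05 and an assumed 95% blinding success for the better device, 80% power is reached at a difference of about 26 points between groups (chi-square) and about 18 to 31 points within participants (McNemar), depending on within-person correlation and on the exact or asymptotic version.*
4. State that a non-significant primary comparison will not be read as showing that a device is indistinguishable, and label the conclusions exploratory.

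If precision for Bang's index is also quoted, give it as an upper limit: a 95% confidence interval half-width of at most 1.96 × √(1/30) = 0.36, about 36 points, near an index of 0. Undecided answers would narrow it.

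Enrolment, procedures and tests do not change. The cost is wording and a less favourable stated figure. The article reports that the trial is recruiting, so the correction can be made before analysis.
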